### 2.5.3 Risks (Thymoglobulin)

Thymoglobulin is indicated for the prophylaxis or treatment of renal transplant acute rejection in conjunction with concomitant immunosuppression. It is contraindicated for in patients with history of allergy or anaphylaxis to rabbit proteins, or who have an acute viral illness.

In a case of anaphylaxis, the infusion should be terminated immediately. Medical personnel should be available to treat patients who experience anaphylaxis. Emergency treatment such as 0.3 ml to 0.5 ml aqueous epinephrine subcutaneously and other resuscitative measures including oxygen, intravenous fluids, antihistamines, corticosteroids, pressor amines, and airway management, as clinically indicated, should be provided.

#### Drug interactions

- Because Thymoglobulin is administered to patients receiving a standard immunosuppressive regimen, this may predispose patients to over-immunosuppression.
- Thymoglobulin can stimulate the production of antibodies which cross-react with rabbit immunoglobulins.

Thymoglobulin is contraindicated in patients with history of allergy or anaphylaxis to rabbit proteins, or who have an acute viral illness.

Anaphylaxis has been reported with Thymoglobulin use. In such cases, the infusion should be terminated immediately.

Thrombocytopenia or neutropenia may result from cross-reactive antibodies and is reversible following dose adjustments.

To minimize first dose effects premedication with corticosteroids, acetaminophen, and/or an antihistamine is recommended.

Prolonged use or overdosage of Thymoglobulin in association with other immunosuppressive agents may cause over-immunosuppression resulting in severe infections and may increased the incidence of lymphoma or post-transplant lymphoproliferative disease (PTLD) or other malignancies. Appropriate antiviral, antibacterial, antiprotozoal, and/or other antifungal prophylaxis is recommended.

During Thymoglobulin therapy, monitoring the lymphocyte count may help to assess the degree of T-cell depletion. For safety, WBC and platelet counts should also be monitored.

The carcinogenic and mutagenic potential of Thymoglobulin and its potential to impair fertility have not been studied.

Animal reproduction studies have not been conducted with Thymoglobulin. It is also not known whether Thymoglobulin can cause fetal harm or can affect reproduction capacity. Thymoglobulin should be given to a pregnant woman only if clearly needed.

#### **2.5.4 Benefits (Thymoglobulin)**

Thymoglobulin is a polyclonal anti-thymocyte globulin, obtained by immunization of rabbits with human thymocytes. Thymoglobulin contains cytotoxic antibodies directed against antigens expressed on human T-lymphocytes. After transplantation these are mostly T-lymphocytes that recognize the foreign antigens carried by the graft.

Immunosuppressive treatment with Thymoglobulin for 7-14 days following renal transplantation decreases the incidence of acute rejection compared to conventional triple drug therapy. This reduction in rejection rate is not associated with an increase in side effects due to (over)immunosuppression.

#### **2.6 Confirmation**

With the signature on page „Responsibilities“ the responsible persons for this clinical trial confirm to conduct the trial in compliance with the protocol, ICH-GCP, the applicable regulatory requirements, and the Declaration of Helsinki (enclosure 1).

### 3. TRIAL OBJECTIVES AND PURPOSE

Reflecting the last decades of clinical organ transplantation the accompanying immunosuppressive therapy developed from single and double to triple, quadruple, or sequential strategies using high-dose or low-dose regimens (6, 12, 13, 19, 21).

Recent multi-drug immunosuppressive protocols attempt to combine the advantage of different mechanisms of action by blocking signal or activation pathways of immunocompetent cells with a dose reduction of each single drug to decrease side effects (5).

Despite all these advantages rejections of allografts - especially steroid resistant rejections (SRR) - do occur and remain one of the major reasons for graft loss and patient death. Undoubtedly one of the most powerful weapons to treat rejection episodes are anti-lymphocytotoxic immunoglobulin preparations (7, 17), a treatment that is generally accepted worldwide for this indication.

The use of immunoglobulins (Ig) in prophylaxis is still in ongoing controversial discussion. The benefit of reducing the incidence of rejections, early graft loss, and dialysis after transplantation, in patients receiving Ig-induction therapy (2) faces arguments regarding necessity of general Ig-induction therapy, the waste of efficacious drugs for the management of SRR, higher rate of infections, and the costs of the treatment (23).

Considering only high-risk patients (i.e., patients who lost their graft due to immunological reasons or patients with high levels of panel reactive antibodies) an Ig-induction therapy is widely accepted, setting the costs of the therapy in relation to the improved outcome of these patients.

Nevertheless, it is desirable to reduce the costs furthermore. A possible way to save money might be the strategy of KADEN et al., who published his experience with a single bolus ATG-Fresenius S therapy in non-sensitised patients 1992 (8).

The bolus ATG protocol cannot, however, be adapted without further investigation, since another report (24) mentions a relatively high incidence of graft vascular thrombosis in patients who received a single high dose of ATG from another manufacturer.

This fact and the results from the references in chapter 2 formed the idea to investigate a study to obtain preliminary information on the safety and efficacy of two induction treatment protocols – ATG-Fresenius S as a bolus regimen and Thymoglobulin in standard application – in immunological risk patients under basal immunosuppression with Tacrolimus, MMF and steroids used in the prevention of acute rejection following renal transplantation.

All AE will be documented but not all AE's will be classified as primary endpoint.

The trial will be performed as a pilot trial to compare tolerance, side effects and efficacy of ATG-Fresenius S compared to Thymoglobulin.

Clinical equivalence of ATG-Fresenius S to Thymoglobulin will be assumed up to a difference rejection in rates of  $\pm 15\%$  absolute.

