**Two immunosuppressive protocols will be compared:**

1. a regimen consisting of a triple drug therapy with Tacrolimus, MMF, and steroids as basis therapy plus IVIG for 5 days (total dose 2g/kg bw, max. 140g). In addition, the patients receive intra-operative 9 mg/kg bw ATG-Fresenius S (completed before reperfusion), followed by 3 mg/kg bw/d for the next 4 consecutive days.

vs.

2. a regimen consisting of a triple drug therapy with Tacrolimus, MMF, and steroids as basis therapy plus IVIG for 5 days (total dose 2g/kg bw, max. 140g). In addition, the patients receive intra-operative 1.5 mg/kg bw Thymoglobulin (completed before reperfusion), followed by 1.5 mg/kg bw/d for the next 3 consecutive days.

After kidney transplantation in end stage renal disease patients it is assumed that:

- the safety profile of ATG-Fresenius S may be superior to that of Thymoglobulin
- the efficacy profile of both treatments is clinically equivalent

The aim is to obtain preliminary information on the safety and efficacy of two induction treatment protocols – ATG-Fresenius S and Thymoglobulin – in immunological high risk patients under basal immunosuppression with Tacrolimus, MMF and steroids used in the prevention of acute rejection following renal transplantation.

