## **4. TRIAL DESIGN**

### **4.1 Type of study, description of study design**

The trial is planned as a multicenter, 1:1 randomised, parallel group, comparative, open study. The study may be expanded to other Swiss or a foreign state centers. The patients included into the study will receive standard immunosuppression therapy consisting of Tacrolimus / MMF / steroids / IVIG / ATG-Fresenius S bolus therapy in one arm and in the other arm Tacrolimus / MMF / steroids / IVIG / Thymoglobulin, respectively.

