## 9. STATISTICS

In this pilot study all statistical analyses will be descriptive and p-values will be interpreted accordingly. Confidence intervals will be provided to assist the interpretation of the observed effects.

The primary analysis of safety will assess the incidence of adverse drug reactions (ADRs) attributable to the investigational treatments according to the causality assessment detailed in Section 7.3, paragraph G. A separate analysis will be performed for each of the ADRs listed in Section 4.3.1 as well as for a summary of all ADRs not included in this compilation.

For comparison between ATG and Thymoglobulin the risk ratio (ratio of proportions of patients reporting a particular ADR at least once under trial drug and reference treatment) and the risk difference (difference between proportions) will be determined, including their 95% confidence intervals determined according to the method described by Newcomb (25). For comparisons between the AE rates under both treatments, descriptive two-sided p-values will be determined with Fisher's exact test. In a working definition, the following findings will be considered to be indicators of a potentially meaningful treatment group difference regarding ADR incidence:

- two-sided p-value  $\leq 0.15$  for the comparison of AE rates,
- risk ratio  $\geq 0.5$  or  $\leq 2.0$ ,
- 95% confidence interval for a risk ratio which excludes the value 1.0, and
- 95% confidence interval for a risk difference which excludes the value 0.0.

All analyses of safety will be performed primarily in the safety data set which includes all patients who have received the investigational treatment at least once. To assess potential bias introduced by premature withdrawal from the trial a sensitivity analysis will be performed in a subset which includes all patients who complete the follow-up period as scheduled (but independently of the presence or absence of protocol violations).

For the analysis of treatment efficacy actuarial life tables will be computed for the following parameters: graft survival, patient survival, time to first rejection episode. All life tables will be based on a period of observation of 24 months.

---

 Relevance criteria derived from (26).

In addition, inferential statistics will be computed for the following parameters:

- Time to 1st and 2nd rejection (Mann-Whitney U-Test).
- Incidence of rejection episodes (Chi-square statistic).

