- Number of rejections per patient (Mann-Whitney U-Test).
- Duration of rejection episodes (t-test).
- 12, and 24-months graft survival rate (Chi-square statistic).
- 12 and 24-months patient survival rate (Chi-square statistic).
- Number of prednisone pulses within 12 and 24 months (Mann-Whitney U-Test).
- Rejection reversal rate (Chi-square statistic).

The analysis of efficacy will be based on the full analysis set (FAS) which includes all patients who were randomized and treated and for whom any post-treatment efficacy data are available.

After completion of the 24-months follow-up period the final biometrical analysis will be performed.

Furthermore, all patient data recorded in the trial database will be tabulated by treatment group using methods of descriptive data analysis, with specification of summary statistics applicable to their levels of measurement.

Sample size estimation:

In this pilot study the determination of the sample sized is based primarily on feasibility rather than on statistical reasons. A total of 40 (Zürich 20, Basel 20) randomised and treated patients (20 in each treatment group) will be included.

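### The ±15-point equivalence rule for rejection has no stated criterion, is not used in Section 9, and cannot credibly be met with 20 patients per arm

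*Protocol*

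**What the plan says.** Section 3 of the protocol states that "Clinical equivalence of ATG-Fresenius S to Thymoglobulin will be assumed up to a difference rejection in rates of" ±15% absolute. It gives no confidence level, and it does not say whether the observed difference or an interval must lie within that range. Further on, the same section lists as an assumption that "the efficacy profile of both treatments is clinically equivalent".

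Section 9 sets the general tone: "In this pilot study all statistical analyses will be descriptive and p-values will be interpreted accordingly". It adds: "Confidence intervals will be provided to assist the interpretation of the observed effects". A method and level (Newcombe, 95%) are named only for the comparisons of adverse drug reactions. For rejection, the list of inferential statistics has "Incidence of rejection episodes (Chi-square statistic"), with Mann-Whitney tests for time to rejection and number of rejections, and life tables for time to first rejection. The ±15-point margin does not appear in Section 9.

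On sample size, Section 9 says that "the determination of the sample sized is based primarily on feasibility rather than on statistical reasons", and "A total of 40 (Zürich 20, Basel 20) randomised and treated patients (20 in each treatment group) will be included". Section 4.2 does not allow drop-outs to be replaced after randomisation.

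**The concern.** A margin only means something with a rule that ties it to the data, and here the rule is missing. Two readings are open, and both fail.

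- If an interval must lie inside ±15 points, the sample is far too small for that to happen at any realistic rejection rate.
- If the observed difference alone decides, or a non-significant chi-square is taken as agreement, equivalence will often be declared when the true rates differ by the margin or more.

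The rationale in Section 3 is a possibly better safety profile at equivalent efficacy. An unsupported equivalence statement on rejection would undercut the efficacy half of that message, in recipients selected for donor-specific antibodies.

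**Working it through.** The protocol gives no power or equivalence calculation, so there is no figure of its own to reproduce.

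**Inputs.** Margin ±15 points (Section 3). n = 20 per arm (Section 9). Interval: Newcombe 95%, borrowed from the adverse drug reaction paragraph of Section 9, with 90% as the alternative (two one-sided tests at 5%). Rejection rates cited in Section 2.2.4 run from 12.5% to 67%; the two product comparisons that give rates for both arms show 58% v 67% and 12.5% v 24%.

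**1. Interval reading.** For x events among n, the Wilson limits are [x + z²/2 ± z√(x(n−x)/n + z²/4)] / (n + z²). The Newcombe limits for d = p1 − p2 are d − √((p1−l1)² + (u2−p2)²) and d + √((u1−p1)² + (p2−l2)²).

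For 0/20 v 0/20 the upper Wilson limit is z²/(n + z²) = 3.8415/23.8415 = 0.161, so the interval is ±16.1 points. Equal outcomes give these half-widths:

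| Events per arm | 95% | 90% |
|---|---|---|
| 0 v 0 | 16.1 | 11.9 |
| 1 v 1 | 19.1 | 15.1 |
| 4 v 4 (20%) | 24.7 | 20.8 |
| 6 v 6 (30%) | 26.8 | 22.9 |
| 10 v 10 (50%) | 28.4 | 24.4 |

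Across all 21 × 21 = 441 possible outcomes:

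- 95% Newcombe: none lies inside ±15 points. Even 0 v 0 needs z²/(n + z²) < 0.15, that is n > 3.8415 × 0.85/0.15 = 21.8, so at least 22 per arm.
- 90% Newcombe: only 0/20 v 0/20 and 20/20 v 20/20 qualify. With a true rate of 12.5% in both arms, the lowest rate cited, the chance of no rejection at all is 0.875^40 = 0.5%.
- Other methods: the 95% Miettinen-Nurminen and Farrington-Manning intervals admit none. The 95% Agresti-Caffo interval admits the same two extremes, and at 90% also 1 v 1 and 19 v 19. Wald, unreliable at such counts, admits only outcomes of 0–1 or 19–20 events in both arms.

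**2. Point-estimate reading.** Fifteen points of 20 patients is 3 patients, so the rule is |x1 − x2| ≤ 3. Exact binomial probabilities that it is met (true rates assumed for illustration):

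- 20% v 20%: 84%
- 35% v 20%, exactly on the margin: 56%
- 40% v 20%, beyond the margin: 42%

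As an example, 10/20 v 7/20 has an observed difference of 15 points and meets the rule. Its 95% Newcombe interval runs from −14.6 to +41.2 points.

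**3. Non-significant chi-square.** At an assumed two-sided 5% level, enumeration gives a non-significant result in 81% of trials at 35% v 20% and in 71% at 40% v 20%. Failing to reject says little about equivalence here.

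**4. Scale.** With equal true rates p and 80% power, n per arm = 2p(1−p)(z(1−α) + z(0.90))²/0.15². With α = 0.025 per side, the squared term is (1.960 + 1.282)² ≈ 10.51. At p = 12.5% this gives 103 per arm, and at p = 58% it gives 228. With α = 0.05 per side the figures are 84 and 186.

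**The case against.** The trial is openly a descriptive pilot, sized on feasibility, with safety as its primary endpoint and rejection secondary. Section 9 promises confidence intervals for observed effects, and details for a secondary endpoint may sit in an analysis plan that is not shown. The efficacy statement in Section 3 is worded as an assumption, with no null hypothesis, error rate or power attached. The two background comparisons that give rates for both products differ by 9 and 11.5 points, both inside the margin.

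Much of this stands and limits the point. Three stronger readings are tempting, and the documents do not support them:

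- *No possible result could show equivalence.* This is exact for the 95% Newcombe interval and some other 95% methods. The protocol fixes no method or level for rejection, and a 90% interval admits 0/20 v 0/20 and 20/20 v 20/20. On the point-estimate reading many results would qualify.
- *Section 9 offers nothing but a test of difference.* That is true of the tests, but it leaves out the general promise of intervals and the descriptive status of every analysis.
- *Equivalent efficacy is a formal trial hypothesis.* The text calls it an assumption, and no sample size or primary conclusion rests on it.

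What the pilot label does not do is cancel the sentence in Section 3. A study that disclaims inference should not also carry a rule under which equivalence is assumed. An analysis plan could supply a method, but it could not make 20 per arm sufficient at the rates cited.

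**Conclusion.** The equivalence sentence in Section 3 is wrong as written and should be corrected. It states a margin and a conclusion without a criterion, and Section 9 does not connect to it. At 20 per arm the 95% Newcombe interval can never lie inside ±15 points; at 90% it can do so only when no patient or every patient has a rejection, which is implausible at cited rates of 12.5% to 67%. Read as a point-estimate rule, it declares equivalence in 56% of trials at a true 15-point difference and in 42% at a 20-point difference.

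The results rest on 20 evaluable patients in each arm, which is the most that Section 9 provides for. Section 4.1 allows further centres, but no larger total is stated. They also rest on carrying the Newcombe method over from the safety analysis, and on true rates chosen for illustration. The defect is one of wording on a secondary endpoint; the primary safety analysis is unaffected.

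**What to change.** In Section 3, delete the equivalence sentence, or relabel ±15 points as a descriptive reference value only. Say that equivalent efficacy is an assumption that this pilot does not test.

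In Section 9, add to the efficacy analyses wording such as:

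> The difference in rejection rates between the groups will be reported with its 95% Newcombe confidence interval. Neither an observed difference within ±15 points nor a non-significant chi-square result will be reported as equivalence.

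If an expected precision is quoted, say that the half-width is about 25 to 28 points for equal rates of 20% to 50%, and narrower at lower rates.

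The cost is a protocol wording change, with no extra patients, visits or data. The sponsor gives up an equivalence statement that the data could not support.

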**Two immunosuppressive protocols will be compared:**

1. a regimen consisting of a triple drug therapy with Tacrolimus, MMF, and steroids as basis therapy plus IVIG for 5 days (total dose 2g/kg bw, max. 140g). In addition, the patients receive intra-operative 9 mg/kg bw ATG-Fresenius S (completed before reperfusion), followed by 3 mg/kg bw/d for the next 4 consecutive days.

vs.

2. a regimen consisting of a triple drug therapy with Tacrolimus, MMF, and steroids as basis therapy plus IVIG for 5 days (total dose 2g/kg bw, max. 140g). In addition, the patients receive intra-operative 1.5 mg/kg bw Thymoglobulin (completed before reperfusion), followed by 1.5 mg/kg bw/d for the next 3 consecutive days.

After kidney transplantation in end stage renal disease patients it is assumed that:

- the safety profile of ATG-Fresenius S may be superior to that of Thymoglobulin
- the efficacy profile of both treatments is clinically equivalent

The aim is to obtain preliminary information on the safety and efficacy of two induction treatment protocols – ATG-Fresenius S and Thymoglobulin – in immunological high risk patients under basal immunosuppression with Tacrolimus, MMF and steroids used in the prevention of acute rejection following renal transplantation.

## **4. TRIAL DESIGN**

### **4.1 Type of study, description of study design**

The trial is planned as a multicenter, 1:1 randomised, parallel group, comparative, open study. The study may be expanded to other Swiss or a foreign state centers. The patients included into the study will receive standard immunosuppression therapy consisting of Tacrolimus / MMF / steroids / IVIG / ATG-Fresenius S bolus therapy in one arm and in the other arm Tacrolimus / MMF / steroids / IVIG / Thymoglobulin, respectively.

### **4.2 Randomisation**

To avoid bias due to patient selection the patients will be assigned to the investigational treatments by randomization. Patients will be assigned a consecutive number in the order in which they enter the trial. The assignment of consecutive numbers will be done within each participating center. Each center will receive a set of sealed random code envelopes which will be labelled with an identification of the trial and a unique treatment number and will contain a note with the identity of treatment assigned to this number. After a patient has been included into the trial, his/her eligibility has been confirmed and he/she is ready to receive the investigational treatment, the investigator will break the seal of the envelope bearing the lowest available number and will administer the treatment corresponding to the included note. The random code envelope must not be opened before the eligibility of a patient has been finally determined and he/she is ready for treatment. Details will be given to the participating investigators.

Patient population:

Recipients, who are at least 18 years or older and have a high immunological risk defined by:

The presence of at least one donor-specific antibody (class I and/or II) detected and specified by flow-technology (FlowPRA and single antigen Flow-beads), which are

- For class I below the threshold of detection of a current CDC T-cell- and B-cell cross-match
- For class II below the threshold of detection of a current CDC B-cell cross-match

Screening failure (Drop-out)

Patients can be replaced by new patients before being randomised. After the randomisation has been performed a replacement of a drop-out is not allowed. Every patient that has been randomised and included in the study will be considered at least in the safety analysis.

To ensure an unbiased assessment of AEs a blind cross-over evaluation of all events will be done. The physicians in Basel will assess the causal relationship of AEs to the investigational treatment in patients treated in Zürich and *vice versa*. The appraisal will be done provided by the treatment e.g. either with ATG-Fresenius S or Thymoglobulin but without knowing.

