**6.3. Diagnosis and treatment of rejection episodes**

Clinical acute rejection episodes are defined by an increase of serum creatinine of >20% from baseline with consisting histology classified according to local practice.

Subclinical acute rejection episodes are defined by a protocol biopsy with consisting histology classified according to local practice.

The treatment of rejections is ad libidum of the physician, however, a cross-over treatment as rescue-therapy by using the immunoglobulin preparation (AFG-Fresenius S or Thymoglobulin) from the other group is prohibited.

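### Patients are randomised within centre but compared with centres pooled, which loses precision to the extent that centres differ in event rates

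*Protocol*

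**What the plan says.** **Randomisation.** Protocol Section 4.1 describes a "multicenter, 1:1 randomised, parallel group, comparative, open study". Section 4.2 adds that "The assignment of consecutive numbers will be done within each participating center" and that "Each center will receive a set of sealed random code envelopes". Centre is therefore a stratum of the randomisation. No block size and no balance of arms within a centre is stated.

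**Size.** Section 9: "A total of 40 (Zürich 20, Basel 20) randomised and treated patients (20 in each treatment group) will be included". This fixes the two margins, 20 per centre and 20 per arm, but not the arm-by-centre split. The "determination of the sample sized is based primarily on feasibility rather than on statistical reasons".

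**Analysis.** For each adverse drug reaction, Section 9 names a risk ratio and a risk difference with Newcombe 95% intervals. For adverse event rates, "descriptive two-sided p-values will be determined with" Fisher's exact test. For efficacy it names chi-square tests, Mann-Whitney tests, a t-test and life tables. None of these uses centre as a stratum or covariate. All analyses are called descriptive.

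**Where centres could differ.** Section 4.2: "The physicians in Basel will assess the causal relationship of AEs to the investigational treatment in patients treated in Zürich", and the reverse for Basel patients. In Section 6.3 both clinical and subclinical rejection rest on "consisting histology classified according to local practice". Section 6.2 lists protocol biopsies under optional monitoring.

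**The concern.** When allocation is done separately within groups, the usual practice is to compare the arms within those groups. If centre predicts the outcome, a pooled comparison leaves the between-centre variation in the error term, although the design would allow it to be removed.

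Centre could predict the outcome here. The primary safety analysis counts events by their causality rating, and each centre's events are rated by physicians of the other centre, so rater group and centre cannot be separated. A stricter rater group would lower the attributable rate of one whole centre. For rejection, classification and the uptake of optional biopsies may vary by site.

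The quantities affected are the ones Section 9 relies on. Intervals are meant to support interpretation, and a potentially meaningful difference is flagged by p at or below 0.15 and by intervals that exclude no effect. With 40 patients and a size set by feasibility, the analysis is one of the few remaining sources of precision.

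**Working it through.** **Inputs from the protocol (Sections 4.1, 4.2 and 9):** 1:1 allocation, 20 per arm, 20 per centre, 95% intervals, two-sided Fisher test with a flag at p ≤ 0.15. The total has no power inputs, so only its sum can be checked: 20 + 20 = 40, which agrees.

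**Assumptions:** the centre event rates, because the protocol gives none, and in steps 1 and 2 exactly 10 per arm per centre.

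**Step 1, interval width with no treatment effect.** Let p be the overall rate and p1, p2 the centre rates.

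- Pooled half-width = 1.96 × √(2p(1−p)/20)
- Stratified half-width = 1.96 × √(2w/20), where w is the mean of p1(1−p1) and p2(1−p2)

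At 30%/70%: pooled 1.96 × √(2 × 0.25/20) = 0.310; stratified 1.96 × √(2 × 0.21/20) = 0.284; ratio √(0.25/0.21) = 1.09.

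**Step 2, false-flag rates under the same balance.** The number of events per arm is a sum of two binomials, one per centre. Enumerating it exactly gives the last two columns.

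| Centre rates | Half-width pooled vs stratified (points) | Excess width | Fisher p ≤ 0.15 | Newcombe interval excludes 0 |
|---|---|---|---|---|
| 50%/50% | 31.0 vs 31.0 | 0% | 8.1% | 4.3% |
| 40%/60% | 31.0 vs 30.4 | 2% | 7.5% | 3.8% |
| 30%/70% | 31.0 vs 28.4 | 9% | 5.6% | 2.6% |
| 20%/80% | 31.0 vs 24.8 | 25% | 2.9% | 1.1% |

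The reference for the Fisher column is 8.1%, not 15%, because the exact test is already conservative with equal centres.

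**Step 3, the same without balance within centre.** Keep 20 per arm and 20 per centre but leave the arm-by-centre split to chance. Fisher p ≤ 0.15 then occurs in 8.1% (equal centres), 8.1% (30%/70%) and 8.2% (20%/80%). The fall seen in step 2 disappears.

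**Step 4, sensitivity.** Simulation, 8,000 runs per scenario, 40% overall rate, true risk difference 0.30. Stratified means a Newcombe interval with Mantel-Haenszel weights and an exact stratified test.

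| Centre rates, lists | Mean interval width, pooled vs stratified | p ≤ 0.05 | p ≤ 0.15 |
|---|---|---|---|
| 40%/40%, balanced | 0.528 vs 0.516 | 37.8% vs 36.5% | 58.0% vs 58.3% |
| 30%/50%, balanced | 0.528 vs 0.505 | 37.6% vs 40.0% | 58.3% vs 59.5% |
| 20%/60%, balanced | 0.530 vs 0.472 | 35.8% vs 44.5% | 57.5% vs 65.2% |
| 20%/60%, simple | 0.533 vs 0.480 | 40.2% vs 48.1% | 61.1% vs 69.1% |

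About 2% of the narrowing comes from the stratified interval method itself, since it also appears with equal centres. At 20%/60% with balanced lists, pooled coverage is 97.3% with no true difference and 96.8% with a difference of 0.30. With simple randomisation it is 94.7% to 94.8%. Precision is therefore lost either way, but over-coverage appears only with balance.

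**Step 5, chance imbalance, possible only without balance.** Suppose one arm has 12 patients from the 70% centre and 8 from the 30% centre, and the other arm the reverse. With no treatment effect, the expected rates are (12 × 0.7 + 8 × 0.3)/20 = 54% and (8 × 0.7 + 12 × 0.3)/20 = 46%. That is an 8-point difference due to centre alone.

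**Step 6, rare reactions.** At a 5% overall rate, even the extreme 0%/10% gives √(0.0475/0.045) = 1.027, or 2.7% excess width. At 10% overall, 0%/20% gives √(0.09/0.08) = 1.061, or 6.1%.

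**The case against.** - **Large centre gaps are assumed.** No document gives centre rates. Eligibility and regimens are common to both centres, and several primary components rest on numerical or administrative criteria. Probable, possible and unlikely all count as attributable, so raters change the outcome only at the border with no relationship or assessment impossible. Section 4.3.2 asks for Banff typing of rejection, although Section 6.3 leaves classification to local practice, and rejection is a secondary endpoint. This stands: a centre effect is possible, not shown to be likely, and a 20-point gap costs only about 2% in width.
- **A reader might infer that the planned intervals and tests are miscalibrated.** The protocol does not support that. Over-coverage needs arms balanced within centre, and Section 4.2 states no blocks. Without balance, calibration is nominal.
- **A reader might count both over-wide intervals and chance imbalance as harms.** They are alternatives: balance gives the first and excludes the second, and lack of balance does the opposite.
- **The trial is a descriptive pilot.** There is no confirmatory error rate and no power target. Pooling does not bias the comparison in expectation or inflate false positives. A statistical analysis plan, not shown, could add centre-adjusted results. This limits the weight of the point, but Section 9 already names the methods and bases its flags on them.
- **Stratifying has limits.** With equal centres it gains nothing and can lose slightly (37.8% vs 36.5% in step 4). With sparse events the risk ratio can be undefined. Both are accepted in the fix.

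**Conclusion.** The mismatch is in the text: allocation is done within centre, and no comparison in Section 9 uses centre. The supported consequence is a loss of precision if centres differ. Around a 50% event rate it amounts to about 2%, 9% and 25% excess interval width at centre gaps of 20, 40 and 60 points, and nothing with no gap. At 20%/60% with a true difference of 0.30, the chance of reaching the p ≤ 0.15 flag is about 8 percentage points lower, with or without balanced lists. These sizes rest on assumed rates.

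It does not follow that the planned analysis is invalid, or that its intervals are certainly too wide in the sense of coverage above 95%. That, and the fall of the Fisher flag rate from 8.1% to 5.6% or 2.9%, holds only for lists balanced within centre. If the split is left to chance, what remains is the lost precision and the possibility that an uneven split mixes rater effects with treatment. The sample size is unaffected. This is a modest point, worth acting on because the remedy needs no new data.

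**What to change.** In Section 9, add these analyses, stratified by randomising centre, and report the crude results beside them:

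- **Proportions:** Mantel-Haenszel risk difference and risk ratio with stratified 95% intervals, and an exact stratified Cochran-Mantel-Haenszel test.
- **Comparisons where Mann-Whitney is named:** the van Elteren test. Whether a rank test suits time to rejection is a separate question.
- **Small added centres:** pool very small ones into one stratum.
- **Sparse events:** rely on the risk difference and the exact test where the risk ratio is undefined.

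State in Section 4.2 whether the envelope lists are balanced within centre, so that the calibration of the crude results can be judged.

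The cost is a few lines of text and no new data, because patients are already numbered by centre. The downside is little or no gain, and a very slight loss of power, if centres are alike or events are rare.
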